**Fig. 1 Fig1:**
[figure not shown]
Schematic chart of the process of the clinical trial. *Abbreviations*: *ABC*^*1*^ Autism Behavior Checklist, *ABC*^*2*^ Aberrant Behavior Checklist, *ACER* Average cost-effectiveness ratio, *ACUR* Average cost-utility ratio, *AE* Adverse event, *ANCOVA* Analysis of covariance, *ASD* Autism spectrum disorder, *CARS* Childhood Autism Rating Scale, *CBA* Cost-benefit analysis, *CEA* Cost-effectiveness analysis, *CHQ-PF28* Child Health Questionnaire-Parent Report Form 28, *CUA* Cost-utility analysis, *EQ-5D-Y* EuroQoL Five-dimension Five-level Youth, *FAS* Full analysis set, *ICER* Incremental cost-effectiveness ratio, *IRB* Institutional review board, *K-CTC* Korean Medicine Clinical Trial Center, *K-PSI-SF* Korean Parenting Stress Index Short Form, *PDD* Pervasive developmental disorder, *PPS* Per protocol set, *PSI* Parenting Stress Index, *RCT* Randomized controlled trial, *SAS* Safety Assessment Set, SMS Social Maturity Scale, *TCM* Traditional Chinese Medicine,*UGSJB* Ukgansangajinpibanha

**Fig. 2 Fig2:**
[figure not shown]
Schedule of enrolment, interventions, and assessments. *Abbreviations*: *ABC*^*1*^ Autism Behavior Checklist, *ABC*^*2*^ Aberrant Behavior Checklist, *CARS* Childhood Autism Rating Scale, *CHQ-PF28* Child Health Questionnaire-Parent Report Form 28, *EQ-5D-Y* EuroQoL Five-dimension Five-level Youth, *K-PSI-SF* Korean Parenting Stress Index Short Form, *SMS* Social Maturity Scale, *UGSJB* Ukgansangajinpibanha

### Inclusion criteria

Children who are 4 to 6 years oldChildren who have received an ASD-specific medical certificate from their physician (e.g., autistic disorder, Asperger’s syndrome, or PDD-not otherwise specified)CARS score of at least 30 in the screening testWritten informed consent signed by a representative.

### Exclusion criteria

Hereditary syndromes, including Rett syndrome, Down syndrome, or fragile X syndromeOther mental disorders, including selective mutism, attention-deficit/hyperactivity disorder, schizophrenia, or depressive disorderHereditary metabolic diseases, including galactose intolerance, Lapp lactase deficiency, or glucose-galactose malabsorptionRecently operated children, seizures (including epilepsy), generalized infections requiring antibiotics, brain injuries (including cerebral palsy), or severe chronic or terminal illness (including malignancy or tuberculosis)Children who have taken risperidone or aripiprazole or who have stopped taking these medications less than 3 months prior to enrolment in the studyChildren who have taken any Korean medicine in the past month prior to enrolment in the studyAspartate aminotransferase, alanine aminotransferase, blood urea nitrogen, or creatinine level more than three times the normal upper limitHypersensitivity to the test drug or placeboDifficulty in swallowing the test drug or placeboIntolerance or fear of acupunctureHemostatic disordersChildren who had participated in another clinical trial within 1 month of the enrolment dateInability to participate in the trial as determined by the trial director or personnel.

### Interventions

Already-prescribed treatments—including medications such as methylphenidate, haloperidol, and selective serotonin reuptake inhibitors; behavioral and educational interventions such as communication interventions, social skills instruction, and occupational therapy; and complementary and alternative therapies such as music therapy, animal therapy, and transcranial magnetic stimulation—will be continued during the trial. Stopping existing treatments and starting new treatments will be restricted during the trial. The use of risperidone, aripiprazole, and any herbal medicine except UGSJB or placebo will be forbidden. Potassium agents, licorice agents, glycyrrhizinate agents, and diuretic agents which can cause myopathy by pseudoaldosteronism or hypokalemia will be used cautiously only if needed.

After screening, suitable participants will be randomly assigned to the 3.0 g/day UGSJB or placebo group. UGSJB granule is composed of nine herbs: Ban Xia (*Pinellia ternate*), Bai Zhu (*Atractylodes japonica*), Fu Ling (*Poria cocos*), Dang Gui (*Angelica gigas*), Chen Pi (*Citrus unshiu*), Chuan Xiong (*Cnidium officinale*), Diao Gou Teng (*Uncaria sinensis*), Chai Hu (*Bupleurum falcatum*), and Gan Cao (*Glycyrrhiza glabra*) (Table 1). Placebo granule is composed of 0.95 g lactose, 0.4 g corn starch, and 0.15 g caramel pigment to match the UGSJB. UGSJB and placebo granules were manufactured and stored by Kyungjin Pharmaceutical Co., Ltd. (Gyeonggi, Republic of Korea). The solvent used in the extract was purified water, and the ratio of extract to herbal drugs was about 12.2%. Storage, dispensation, and quality control of the UGSJB and placebo granules were carried out by a blinded pharmacist in each study center. Caregivers will be instructed to dissolve in water and administer one pack (1.5 g) of UGSJB or placebo granule after breakfast and dinner for 12 weeks, which was the period that reported effectiveness in previous studies [11, 12]. The dosage regimen was determined by referring to the authorization by the Ministry of Food and Drug Safety and the clinical judgment of Korean medicine doctors. The quantities of marker constituents per pack were 3.99 mg of glycyrrhizinate and 11.18 mg of hesperidin. Lead and microorganisms were not detected, and the concentration of arsenic was 0.33 parts per million in one pack of UGSJB. The UGSJB or placebo will be prescribed by Korean medicine doctors with more than 5 years of clinical experience. If there are any adverse events (AEs) related to UGSJB, such as pseudoaldosteronism, myopathy, allergic skin reaction, and gastrointestinal upset, that participant will stop taking medication and will receive appropriate treatment according to the severity of the AEs. The guardians should return the used as well as unopened packages to check the adherence to treatment.

**Table 1 Tab1:** Composition of Ukgansangajinpibanha granule

Plant name	Used part	Registration	Amount, grams
*Pinellia ternate* Breitenbach (Araceae)	Dried rhizome	KP	0.84
*Atractylodes japonica* Koidz. (Compositae)	Dried rhizome	KP	0.67
*Poria cocos* Wolf (Polyporaceae)	Dried scleorotia	KP	0.67
*Angelica gigas* Nakai (Umbelliferae)	Dried root	KP	0.5
*Citrus unshiu* Markovich (Rutaceae; citrus peel)	Dried fruit peel	KP	0.5
*Cnidium officinale* Makino (Umbelliferae)	Dried rhizome	KP	0.5
*Uncaria sinensis* Havil. (Rubiaceae)	Dried ramulus	KHP	0.5
*Bupleurum falcatum* Linné (Umbelliferae)	Dried root	KP	0.34
*Glycyrrhiza glabra* L. (Leguminosae; licorice)	Dried root and rhizome	KP	0.25

*Abbreviations*: *KHP* Korean Herbal Pharmacopoeia, *KP* Korean Pharmacopoeia.

Scalp acupuncture will be performed in all participants by using six fixed points at GV20 (Bai Hui), GV24 (Shen Ting), and EX-HN1 (Si Shen Cong) in a total of 24 sessions for 12 weeks. We considered participants who attended 75% or more (≥18 of 24) of the acupuncture sessions to have completed a full course of treatment. A 0.25 × 40 mm disposable sterilized stainless-steel needle will be used. GV20 and GV24 were inserted backward and EX-HN1 was inserted outward. After insertion of the needle (10–15 mm of depth), it will be stirred by hand until de qi sensation. The inserted needle will remain for 30 min with available manual stimulation. If the child pulls out the needles during the procedure, other needles will be inserted. Acupuncture will be performed by Korean medicine doctors with 3 years of acupuncture training and more than 1 year of clinical experience. If the participant strongly complains of discomfort, the practitioner will stop the acupuncture procedure.

### Random assignment

Subjects who have agreed to participate in this clinical trial are assigned a screening number in the order of their guardian’s written informed consent. After completing the screening test, eligible subjects will be assigned to the UGSJB or placebo group according to their random assignment code. The random assignment codes are provided by an independent statistician in the Korean Medicine Clinical Trial Center (K-CTC), and random sequence numbers were generated by blockrand package 1.3 of R 3.4.2 (2017-09-28). The block random assignment will be made after stratification according to the hospital so that the subjects of each group are approximately identical.

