### Study participants

One hundred twenty children will be recruited from two hospitals (Kyung Hee University Hospital at Gangdong and Kyung Hee University Medical Center, Republic of Korea) through online and offline recruitment notices, including posters and webpages. Those two hospitals have recruited participants in more than 20 clinical trials that eight studies were completed and 19 studies are recruiting in Kyung Hee University Hospital at Gangdong, and 41 studies were completed and 52 studies are recruiting in Kyung Hee University Medical Center. The participants’ guardians will be provided with research information, such as objectives, procedures, and potential benefits and harms, through standardized interviews. Informed consent will be obtained from children’s guardians prior to the screening process. The participants will be allowed to withdraw from the study at any time. The research procedure will be carried out as shown in Figs. 1 and 2. All participants will undergo a 12-week treatment and 12-week follow-up. After the screening session, children will be scheduled for 24 treatment visits (twice a week) and one follow-up visit (12 weeks after last treatment). Guardians will be sent text messages as reminders of the scheduled visits.

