### Sample size calculation

In Zhou *et al*. (2015) [32], an RCT on autistic children (average age of 4.75 years) was conducted to measure the CARS before and after the interventions in the herbal medicine–plus–behavioral education group and the behavioral education–alone group. The changes in CARS were −7.9 ± 5.42 for combination therapy and −4.6 ± 5.53 for behavioral education alone. For the purpose of calculating the standard deviation of the CARS change, the before-after correlation coefficient was assumed to be 0.33, referring to Sun *et al*. (2016) [33]. The sample size was calculated by using a two-tailed 5% significance level, 80% power, and 1:1 allocation by PASS 14 (NCSS Statistical Software, Kaysville, UT, USA). The alternative hypothesis was established that the change in CARS for 12 weeks between the experimental group and the control group was not the same. The required number of subjects per group is 45, and the total number of enrolled subjects is 120 (60 in each group), allowing for a 25% withdrawal rate.

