### Statistical analysis

Data coding will be kept by the researcher team, and data analysis will be conducted by statisticians who are independent of the research team. Effectiveness data will be analyzed mainly with full analysis set (FAS) and further analyzed with per protocol set (PPS). The FAS is defined as all subjects who have taken at least one prescription in the clinical trial and have at least one measurement of the primary outcome after having the prescription. The PPS is defined as all subjects who have taken more than 118 packs (70% of the total 168 packs). The safety analysis includes all data from the participants who have taken at least one prescription in the clinical trial.

Continuous data will be presented as descriptive statistics such as mean and standard deviation, and any statistical differences between the two groups will be tested by using the independent *t* test or Wilcoxon rank-sum test. Categorical data will be presented as frequency and percentage, and any statistical differences between the two groups will be tested by using the chi-squared test or Fisher’s exact test. If significant differences of baseline are recognized between two groups, analysis of covariance (ANCOVA) or rank ANCOVA will be used. In secondary analyses within groups, continuous data will be analyzed by using the paired *t* test or Wilcoxon signed-rank test, and categorical data will be analyzed by using McNemar’s test.

The significance level is 0.05 for all statistical tests, and two-tailed tests will be performed. Missing values will be imputed by the last-observation-carried-forward method.

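### A free gain in precision: randomisation is stratified by hospital, but the named between-arm tests carry no hospital term

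*Protocol article*

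**What the plan says.** On the design, the Random assignment section states: "The block random assignment will be made after stratification according to the hospital", with the stated aim of making the two groups similar. The Study participants section gives the number of strata: "One hundred twenty children will be recruited from two hospitals".

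On the analysis, the Statistical analysis section fixes the between-arm tests by type of data. For continuous data, "any statistical differences between the two groups will be tested by using the independent *t* test or Wilcoxon rank-sum test". For categorical data, "any statistical differences between the two groups will be tested by using the chi-squared test or Fisher’s exact test". One adjusted analysis is mentioned: "If significant differences of baseline are recognized between two groups, analysis of covariance (ANCOVA) or rank ANCOVA will be used". No covariates are listed for it, and that section does not mention hospital.

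**The concern.** Blocking within hospital makes the arms nearly balanced on hospital, so differences between hospitals largely drop out of the treatment contrast. An unstratified test still counts those differences as error. When hospital is prognostic, the reported standard error is then larger than the true sampling variability of the estimate, and the test rejects less often than its nominal level allows.

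What is at stake is precision. The sample size leaves little margin over 80% power at the planned number of completers, so recovering lost precision at no cost is worthwhile. Model details are often left to a statistical analysis plan. Here, however, the article names the tests, and a plan that followed it faithfully would carry the mismatch forward.

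The conditional ANCOVA would not be expected to close the gap. It is triggered by a significant baseline difference between the arms, and stratified blocking makes such a difference on hospital very unlikely. If another variable triggers it, hospital is still not a named covariate.

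**Working it through.** **Inputs.** From Sample size calculation: "The changes in CARS were −7.9 ± 5.42 for combination therapy and −4.6 ± 5.53 for behavioral education alone", two-sided 5% level, 80% power, 1:1 allocation, 45 per group, enrolled as 60 per group to allow for 25% withdrawal. (The Abstract shows 120 per group; this check uses the Sample size section.) The share of variance in CARS change due to hospital, R², is not in the document. I assume 0% to 20%.

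**The plan's own figure.**
- Difference: 7.9 − 4.6 = 3.3 points.
- Pooled SD: √[(5.42² + 5.53²)/2] = 5.475.
- Exact power of the two-sample t test: 0.798 at 44 per group and 0.807 at 45, so 45 is the smallest number reaching 80%.
- Withdrawal: 45/0.75 = 60 per group, 120 in total.

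The stated figure reproduces, and it is the figure for a test without a hospital term.

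**Overstatement of the standard error.** With n per arm, total variance σ², and arms balanced within hospital, the true variance of the difference is 2σ²(1 − R²)/n. The unstratified test uses about 2σ²/n. The ratio of standard errors is 1/√(1 − R²):
- R² = 0.05: 1/√0.95 − 1 = 2.6%
- R² = 0.10: 1/√0.90 − 1 = 5.4%
- R² = 0.20: 1/√0.80 − 1 = 11.8%

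**What these shares mean in CARS points.** With two equal-sized hospitals, the gap in mean change between them is 2 × SD × √R²:
- 5%: 2 × 5.475 × 0.2236 = 2.4 points
- 10%: 2 × 5.475 × 0.3162 = 3.5 points
- 20%: 2 × 5.475 × 0.4472 = 4.9 points

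**Effect on the test.** Simulation with 20,000 runs per setting, 45 per group, two hospitals of near-equal size (22 and 23 per arm), exact balance within hospital, and total SD held at 5.475. The unadjusted t test is compared with a linear model of arm plus hospital.

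| Assumed share | Gap (points) | SE overstated (formula) | Type I error, unadjusted / adjusted | Power, unadjusted / adjusted | Power forgone (points) |
|---|---|---|---|---|---|
| 0% | 0 | 0% | 0.049 / 0.049 | 0.807 / 0.806 | about 0 |
| 5% | 2.4 | 2.6% | 0.044 / 0.050 | 0.809 / 0.823 | about 1 |
| 10% | 3.5 | 5.4% | 0.037 / 0.047 | 0.818 / 0.846 | about 3 |
| 20% | 4.9 | 11.8% | 0.029 / 0.049 | 0.836 / 0.886 | about 5 |

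The simulated standard errors agree with the formula. At 20%, the mean unadjusted SE is 1.154 against a true sampling SD of 1.028, a ratio of 1.12. The mean adjusted SE is 1.029.

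If all 60 per group were analysed, the same comparison gives power 0.910 against 0.918 at a 5% share, 0.916 against 0.932 at 10%, and 0.929 against 0.958 at 20%.

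**The case against.** The strongest objection is that harm is not shown. The standard error is too large only if hospital predicts CARS change, and nothing in the document says that it does. At a 0% share nothing is lost. The upper shares are also demanding: 10% needs the hospitals to differ in mean change by 3.5 points, more than the whole planned effect of 3.3, and 20% needs about 1.5 times that effect (4.9/3.3). At a 2% share the difference in power is about half a point (0.810 against 0.816). This stands, and it is why the point is conditional and modest.

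A reader might also infer that hospital-specific raters or case mix make a hospital effect likely. The document does not support that. It does not say who rates CARS at each hospital, and it describes no difference in case mix. It cites inter-rater agreement of 0.94 for the Korean CARS. The sample size rests on change scores, in which a stable difference in rater severity would largely cancel. The Discussion does concede that evaluators' subjectivity could affect outcomes, but it does not link this to hospital.

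Two further readings go too far. The first is that every between-arm analysis ignores hospital: the conditional ANCOVA leaves its covariates open, so hospital is not shown to be excluded. The second is that hospital differences cannot reach the treatment estimate: blocking gives approximate balance at randomisation, and withdrawals, or exclusion of children with no post-treatment CARS measurement, can disturb it.

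Finally, the stratification still serves the stated aim of similar groups whatever analysis follows. That is true, but it gives no reason to decline an adjustment that costs almost nothing.

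**Conclusion.** The named tests do not match the stratified randomisation, and adding hospital is a free improvement. It does not correct an invalid analysis. As planned, the treatment estimate is not biased, type I error is at or below 5%, and 45 per group gives at least 80% power. A reader might infer that the planned standard errors are simply wrong, or that the trial is underpowered. Neither follows: the first holds only if hospital is prognostic, and the required sample size does not rise.

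Over the assumed shares of 0% to 20%, the standard error is overstated by 0% to 11.8%, and the power forgone at 45 per group is 0 to about 5 points. The lower part of that range is the easier to believe, given the gaps in CARS points that the upper part needs. These figures rest on two hospitals of about equal size, near balance of arms within each, and 5.475 as the total SD of CARS change, including any difference between hospitals.

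**What to change.** Before unblinding, prespecify hospital as a fixed effect in the primary CARS-change model and in the models for the continuous secondary outcomes. Where a rank test is used, replace the plain Wilcoxon rank-sum with the van Elteren test stratified by hospital. For any categorical comparison between arms, use a Cochran-Mantel-Haenszel test stratified by hospital. This last change matters least, because the primary and secondary outcomes are all scale scores.

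The cost is one degree of freedom, from 88 to 87 at 45 per group or from 118 to 117 at 60 per group. No extra participants, visits or data are needed. If hospital turns out not to matter, power is essentially unchanged (0.806 against 0.807). Fixing the term in advance also removes a later, data-driven choice about whether to adjust for hospital.

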#### Allocation concealment

The independent statistician who generated the random assignment code or a central researcher in K-CTC who does not have contact with the subjects provided the random assignment table directly to Kyungjin Pharmaceutical Co., Ltd., and the company created a label for the medications to be used in the clinical trial. The random assignment code will be kept only by the independent statistician, the central researcher, and the pharmaceutical company personnel during the clinical trial period and will not be disclosed to any subject unless justified by a pre-defined reason.

#### Blinding

Subjects, acupuncturists, data collectors, and statistical analysts will be blinded to which medication will be administered to subjects by using placebo as a control. The placebo will have the same formulation and properties of the UGSJB granule to prevent any bias in safety and efficacy assessments. Unblinding should be considered on a case-by-case basis and only if severe medical emergencies occur or administration information affects the treatment of the subjects.

### Primary outcome measures

#### Childhood Autism Rating Scale

CARS was developed to distinguish autism from other developmental disorders and to assess the severity of autism. It has high reliability, validity, and inter-rater consistency, and a cutoff score of 30 points distinguished autism from other developmental disorders. In addition, CARS reported a high rate of consistency of 92% with experts when used after short training, even if the rater has little experience with autism. In the Korean version of CARS, the internal consistency coefficient (Cronbach’s α) is 0.87, the inter-rater agreement is 0.94, and the test-retest reliability is 0.91 [20]. A total score of 30–37 indicates mild autism, and a total score of 37.5–60 indicates severe autism. In this clinical trial, the assessment will be carried out during the visit at baseline (visit 1), mid-point (visit 14), termination (visit 25), and follow-up (visit 26).

### Secondary outcome measures

#### Autism Behavior Checklist (ABC^1^)

ABC^1^ was developed by Krug *et al*. for differentiating autistic children from intellectual disability, deaf-blind, emotionally disturbed, or normal children [21]. It provides insight into the general characteristics of what an individual looks like compared with another person. ABC^1^ has a reported internal reliability of 0.87 [22], sensitivity of 0.38–0.58, specificity of 0.76–0.97 [23], and test-retest reliability of 0.83 [24]. A child with a total score above 67 is highly likely to be autistic, and those with a total score between 53 and 67 require further evaluation. The assessment will be carried out during the visit at baseline (visit 2), mid-point (visit 14), termination (visit 25), and follow-up (visit 26).

#### Aberrant Behavior Checklist (ABC^2^)

ABC^2^ was developed by Aman *et al*. to measure the treatment effectiveness for people with intellectual disabilities [25] and has been widely used for measuring the progress of treatment for PDD [26]. Cronbach’s α ranges from 0.86 to 0.94, and the inter-rater reliability is 0.63 [27]. Higher scores mean a greater degree of aberrant behavior. The assessment will be carried out during the visit at baseline (visit 2), mid-point (visit 14), termination (visit 25), and follow-up (visit 26).

